### Harms

This pilot implementation component is considered minimal risk for multiple reasons. First, the randomized crossover simulation will involve standardized simulated or deidentified patient cases rather than live clinical encounters. The participants in this simulation component will be health care providers who interact with an EHR interface in a controlled environment. The decision support tool will provide risk estimates and triage recommendations based on synthetic or deidentified data. As such, the simulation component is not expected to pose physical harm, diagnostic error affecting patient care, or adverse clinical outcomes. For the observational/model-development components, adults with PBC will contribute clinical, elastography, and patient-reported outcome data under institutional review board–approved procedures and standard privacy protections.

### Participant Timeline

Participants will enter the study and begin with baseline assessments, which include collection of demographic information, medical history, and initial laboratory values, as well as elastography measurements for liver and spleen stiffness. At this visit, participants will also be enrolled in the PRO system, with instructions for completing the WI-NRS and the PBC-40 questionnaires. These assessments will continue throughout the observation period to capture longitudinal symptom trajectories. The schedule of enrollment, interventions, and assessments is provided in Checklist 1.

Biochemical data will be collected at monthly intervals for the duration of the study, ensuring high-resolution monitoring of disease activity. Elastography will be repeated at predefined intervals, typically every 6 to 12 months or as clinically indicated, to track changes in liver and spleen stiffness over time. Clinical outcomes such as the development of varices, ascites, or hepatic encephalopathy will be monitored continuously through routine clinical care and documented in the study database.

For participants involved in the implementation phase, the timeline includes a randomized crossover simulation in which clinicians will manage deidentified cases under 2 conditions: usual care and CDS-assisted care. This simulation will occur after the development and validation phases are complete. Following the simulation, a pragmatic pilot will be conducted in real-world hepatology clinics, where the CDS tool will be integrated into the EHR and used during routine visits. Clinician usability and trust assessments will be administered at the end of each simulation period and again after the pilot phase.

The overall duration of participation for patients in the observational component is expected to be up to 24 months. Clinicians participating in the implementation evaluation will engage in shorter, structured sessions for simulation and a limited rollout period for the pilot.

### Sample Size and Power Considerations

Because this protocol involves model development, validation, and implementation feasibility, the planned sample size was based on expected cohort availability and anticipated outcome events rather than a conventional hypothesis-testing formula. The sample size determination for this study is primarily driven by the second aim, which focuses on validating the predictive model for CSPH. On the basis of preliminary data and published estimates, we anticipate enrolling approximately 600 patients with PBC across participating sites [7]. This cohort size reflects the expected availability of retrospective and prospective data within the study time frame and ensures adequate representation of key subgroups, including patients with AIH overlap and MASH [19,20].

On the basis of prior PBC cohorts, the prevalence of portal hypertension or CSPH in hepatology referral populations has been reported to range from approximately 24% to 47% depending on disease stage and case mix [25,26]. With a projected sample of 600 participants, this corresponds to an estimated 144 to 282 CSPH events, which provides a sufficient number of outcome events to support model development and validation and evaluate improvements in model discrimination relative to established criteria such as Baveno VII.

In addition, sample size considerations accounted for model complexity. Current methodological guidance for prediction modeling recommends ensuring an adequate number of outcome events relative to the number of predictor parameters to reduce the risk of model overfitting. The anticipated event counts in this cohort are expected to support the planned set of candidate predictors while maintaining an appropriate events-per-predictor ratio for stable model estimation [27].

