### Eligibility Criteria

Adults aged 18 years or older with a confirmed diagnosis of PBC according to American Association for the Study of Liver Diseases criteria (ie, defined as elevated ALP of ≥1.5 times the upper limit of normal in combination with a positive antimitochondrial antibody or disease-specific antinuclear antibodies such as sp100 or gp210) [2]. For individuals who are seronegative, histological confirmation through liver biopsy will be mandatory. All participants must have been receiving standard therapeutic dosing of ursodeoxycholic acid for a minimum of 3 months prior to enrollment, defined as 13 to 15 mg per kilogram of body weight per day administered in 2 or 3 divided doses [2]. Patients who are on second-line therapies, including farnesoid X receptor agonists or peroxisome proliferator–activated receptor agonists, will also be eligible, and therapy class will be recorded as a covariate. Additionally, baseline elastography data, including LSM and SSM, must be available within 6 months of enrollment.

Individuals will be excluded if they have previously undergone liver transplantation or are currently listed for transplantation or if they present with decompensated cirrhosis at baseline, defined as Child-Pugh class B or C [16]. Other exclusion criteria include active malignancy, uncontrolled systemic illness, pregnancy, or inability to provide informed consent. Patients with significant alcohol consumption within 6 months of enrollment (ie, more than 20 grams per day for female individuals or more than 30 grams per day for male individuals or an Alcohol Use Disorders Identification Test–Consumption score of 4 or higher) [17] will not be eligible. Additional exclusions are coexisting chronic liver diseases such as chronic viral hepatitis, hemochromatosis, Wilson disease, or alpha-1 antitrypsin deficiency, as well as active or suspected drug-induced liver injury within the prior 6 months, including drug-induced autoimmune hepatitis (AIH). Any condition deemed by the investigators to compromise participant safety or data integrity will also result in exclusion. A summary of inclusion and exclusion criteria is provided in Textbox 1.

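### The expected 144 to 282 CSPH events carry over an unadjusted referral-population rate for a broader condition, so the count is probably optimistic for the eligible cohort, mainly at its lower end

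*Protocol article*

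**What the plan says.** Under Sample Size and Power Considerations, the protocol article bases the sample size on cohort availability and anticipated outcome events, not on a hypothesis-testing formula, with the second aim as the main driver. It gives the planned size: "we anticipate enrolling approximately 600 patients with PBC across participating sites". It then reports that "the prevalence of portal hypertension or CSPH in hepatology referral populations has been reported to range from approximately 24% to 47" per cent, "depending on disease stage and case mix". The next sentence applies this to 600 participants: "this corresponds to an estimated 144 to 282 CSPH events". It adds that this "provides a sufficient number of outcome events to support model development and validation" and an evaluation of improved discrimination over Baveno VII. The following paragraph relies on the same count for an appropriate ratio of events to predictors.

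Under Eligibility Criteria, and again in Textbox 1, the study excludes patients with "decompensated cirrhosis at baseline, defined as Child-Pugh class B or C" and those who have "previously undergone liver transplantation or are currently listed for transplantation". It also requires that "baseline elastography data, including LSM and SSM, must be available within 6 months of enrollment" and defines the diagnosis in part by an ALP of at least 1.5 times the upper limit of normal.

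**The concern.** Two things change between the sentence that gives the rate and the sentence that uses it.

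- **The condition.** The rate is for portal hypertension or CSPH. The product is labelled CSPH, which is the narrower, clinically significant part.
- **The population.** The rate is for hepatology referral populations and is said to depend on stage. The enrolled cohort has its advanced end removed, and that is where CSPH would be expected to be most common. The sample size section does not mention these exclusions.

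Both changes would be expected to lower the count. This matters because the event count is the quantitative support for the sample size. Three claims rest on it: enough events to develop and validate the model, enough to show better discrimination than Baveno VII, and a safe number of predictors. If the count is too high, all three are weaker than stated, and an upper figure of 282 could be used to justify more candidate predictors than the data can carry.

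**Working it through.** **Inputs from the protocol article.** N = 600; prevalence p = 24% to 47%; stated count 144 to 282 (all from Sample Size and Power Considerations). Exclusions are from Eligibility Criteria.

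**Step 1: reproduce the stated figure.** 600 × 0.24 = 144 and 600 × 0.47 = 282. Both are exact, so the full referral-population rate was carried over with no adjustment.

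**Step 2: allow for the exclusions.** Let f be the share of the source cohorts' cases that this study would exclude. The documents do not give f. Assume that everyone excluded is a case; if some are not, the fall is smaller for the same f. The prevalence among those left is p(1 − f)/(1 − pf), and the expected count is 600 times that.

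For f = 10%:
- Low end: 600 × 0.216/0.976 ≈ 133.
- High end: 600 × 0.423/0.953 ≈ 266.

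**Step 3: allow for the narrower condition.** Let c be the share of the remaining cases that are CSPH. The documents do not give c either. Multiply the count from step 2 by c; 75% is used as an illustration.

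| f (assumed) | Count, c = 100% | Count, c = 75% |
|---|---|---|
| 0% | 144–282 | 108–212 |
| 10% | 133–266 | 100–200 |
| 20% | 121–249 | 91–187 |
| 30% | 109–230 | 81–172 |

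**Step 4: where the loss falls.** At f = 30% and c = 100%, the low end drops by (144 − 109)/144 ≈ 24% and the high end by (282 − 230)/282 ≈ 18%. The low end loses more in relative terms.

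**Step 5: how far the ranges still overlap.** With c = 100%, the adjusted high end falls below 144 only when f exceeds (0.47 − 0.24)/(0.47 × 0.76) ≈ 64%. Over any moderate f, the adjusted range and the stated range overlap widely.

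**Step 6: consequence for the predictor set.** At any fixed ratio of events to parameters, the number of parameters the data support moves in proportion to the events. Against 144 events, 109 supports about 76% as many (109/144) and 81 about 56% (81/144).

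**The case against.** The strongest reply is that the cited cohorts are not at hand. The article says only that the rate varies with stage and case mix. It does not say that the cohorts included decompensated or listed patients. If they were already limited to compensated disease, the population mismatch disappears. The combined label may also mean that one source reported portal hypertension and another CSPH, so the share of the range that is not CSPH is unknown. Other factors could offset the fall: the ALP criterion and the elastography requirement could move prevalence in either direction, and patients free of CSPH at baseline could develop it during the 24-month observation. The figure is also offered as an estimate, and its range already spans a factor of about two.

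Most of this stands, and it limits the point. Four stronger readings are tempting, and the documents do not support them:

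- **That the source cohorts covered all stages.** This is an inference; the article does not describe their stage mix.
- **That this enrolment cannot be expected to yield the stated count.** Step 5 shows wide overlap under moderate assumptions.
- **That 24% should be treated as an upper-side value.** The adjusted high ends in step 2 (230 to 266 events) are well above 144. Nor can a large low-end loss be shown by removing the same share of all patients at both ends: 10% of the cohort is 0.10/0.24 ≈ 42% of cases at the low end but 0.10/0.47 ≈ 21% at the high end, and nothing in the article supports that asymmetry.
- **That a definite amount of power is lost.** For an AUROC of 0.85 against an assumed 0.80, using all 600 patients, illustrative DeLong power at 144 events is 47%, 61% or 82% for an assumed correlation of 0.3, 0.5 or 0.7. The unstated correlation alone moves power by 35 points, so power figures are illustrative only.

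The reply does not remove the mismatch in the text. The article names disease stage as a driver of the rate and then does not account for its own stage restriction. It also changes the name of the condition from one sentence to the next.

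**Conclusion.** The point holds as a mismatch in a figure the sample size section relies on. It is not an arithmetic error. The rate matches neither the eligible population nor the named outcome as stated, and the resulting count is probably optimistic, mainly at its lower end. The direction is likely but not proved. The size depends on two quantities the documents do not give: the share of source cases that would be excluded and the share of the rest that are CSPH. For exclusion shares of 10% to 30%, the low end is about 109 to 133 events if all remaining cases are CSPH, and about 81 to 100 if 75% are. The lower bound of 144 and the unconditional statement that the events suffice are therefore not justified as written.

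**What to change.** Restate the expected count as CSPH only, in patients who meet the eligibility criteria (Child-Pugh A, not listed for transplantation). Take it from a count in the participating sites' electronic records, or from matching subsets of the cited cohorts if those are reported. Alternatively, if the cited rates already apply to such patients and to CSPH alone, say so.

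Until then:
- Present 144 to 282 together with a downward sensitivity range and the assumptions behind it, for example the table above.
- Set the number of candidate predictor parameters by the low end of that range.
- Make the sufficiency statement for development, validation and the Baveno VII comparison conditional on the restated count.

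The cost is one reworded paragraph and a feasibility count, and the article states that recruitment has not begun. The stated event figure may become less favourable. No extra patients are needed for this correction.

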Secondary outcomes will include fairness metrics to ensure equitable model performance across demographic and clinical subgroups, defined as an AUROC parity gap of no more than 5%. Additional exploratory outcomes will examine the impact of the intervention on workflow efficiency and clinician confidence in decision-making.

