### Data Collection

Retrospective data will be sourced from institutional EHRs and data warehouses, capturing historical laboratory values, elastography reports, and clinical outcomes relevant to PBC. Prospective data collection will be conducted in outpatient hepatology clinics using secure, HIPAA (Health Insurance Portability and Accountability Act)-compliant platforms such as REDCap for PROs. These outcomes will include validated instruments such as the WI-NRS, administered twice daily to capture circadian variation in pruritus, and the PBC-40 questionnaire, administered monthly to assess quality of life domains.

Biochemical data, including ALP, bilirubin, aminotransferases, albumin, and platelet count, will be collected at monthly intervals to provide high-resolution longitudinal trajectories. LSM and SSM values will be obtained at baseline and during scheduled follow-up visits, with probe frequency and stiffness values recorded in kilopascals to ensure standardization. Clinical outcomes such as time to variceal development, ascites, and hepatic encephalopathy will be tracked over a 24-month observation period.

All data will be deidentified prior to analysis and stored in secure environments that comply with institutional and federal privacy regulations. Quality control procedures will include automated range checks for laboratory values, standardized reporting templates for elastography, and audit trails for PRO completion. Missing data will be addressed using multiple imputation techniques to minimize bias and preserve statistical power. Data integration will occur through structured pipelines that normalize heterogeneous inputs for use in machine learning models, ensuring consistency across biochemical, imaging, and symptom domains.

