### AI Model Development and Validation

The predictive model will be developed using a prespecified machine learning pipeline. Candidate predictors will include longitudinal biochemical markers, platelet count, LSM, SSM, symptom scores, treatment response status, and relevant comorbidities. Features will be selected based on clinical relevance, data availability, and model stability, with highly collinear or sparsely available variables excluded or combined where appropriate.

The dataset will be divided into training, internal validation, and held-out testing subsets at the patient level to avoid data leakage. Model development will use gradient-boosted ensemble algorithms, with hyperparameters tuned within the training set using cross-validation. External validation will be performed using data from at least one participating site not used during model training where feasible.

Class imbalance will be addressed using strategies applied only within the training data, including class weighting or resampling approaches as appropriate. SHAP values will be generated to provide both patient- and cohort-level feature contributions. Model updating will not be performed during initial validation; if performance drift or poor calibration is observed during prospective deployment, recalibration or updating will be conducted using prespecified procedures and reported transparently.

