## Results

At the time of manuscript submission, this protocol had not yet begun participant recruitment or data analysis. No participants had been recruited. The study did not receive external funding; therefore, no funding date is applicable. Data collection is projected to begin after institutional review board approval and ClinicalTrials.gov registration, with retrospective data extraction and prospective observational data collection expected to occur over approximately 24 months. The clinician-level randomized crossover simulation and pragmatic pilot implementation phases are expected to occur after model development and validation are completed. Data analysis will begin after completion of the relevant data collection phases. The main study findings are expected to be submitted for publication in summer 2029.

The integrated disease activity index is expected to show strong calibration with established prognostic scores and greater responsiveness to clinically meaningful changes, whereas the inclusion of PROs will provide a more comprehensive view of symptom burden. The predictive model is expected to achieve an AUROC of at least 0.85 for identifying CSPH and deliver a net reclassification improvement of 10% or more over Baveno VII criteria, reducing unnecessary endoscopies without compromising safety. Finally, the CDS prototype is expected to improve clinician adherence to guideline-concordant care pathways, reduce decision time, and achieve high usability and trust scores during the simulation and pilot phases.

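### The 144 to 282 CSPH events that justify the sample size are prevalent cases in the whole cohort: not a count of incident complications, and not available in full for held-out validation

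*Protocol article*

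**What the plan says.** Sample Size and Power Considerations ties the sample size mainly to validating the Aim 2 model. It states that "we anticipate enrolling approximately 600 patients with PBC across participating sites", drawn from retrospective and prospective data, and that "the prevalence of portal hypertension or CSPH in hepatology referral populations has been reported to range from approximately 24% to 47" percent. It concludes: "With a projected sample of 600 participants, this corresponds to an estimated 144 to 282 CSPH events". It calls this number sufficient to develop and validate the model and to assess gains in discrimination over Baveno VII, and then relies on it for an adequate ratio of events to predictors.

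The Aim 2 target is described in more than one way:

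- The Objective in the Abstract and the Statistical Analysis section refer to complications of CSPH.
- The Outcomes section names CSPH together with early complications, giving variceal hemorrhage and ascites as examples.
- The Results section sets its benchmark, an AUROC of at least 0.85, for CSPH itself.

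On follow-up, Data Collection says: "Clinical outcomes such as time to variceal development, ascites, and hepatic encephalopathy will be tracked over a 24-month observation period". On the use of the data, AI Model Development and Validation says: "The dataset will be divided into training, internal validation, and held-out testing subsets at the patient level". It gives no fractions, and adds external validation at one or more sites where feasible. Eligibility Criteria exclude patients "if they present with decompensated cirrhosis at baseline, defined as Child-Pugh class B or C", but not patients with CSPH or varices at entry.

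**The concern.** A prevalence multiplied by a sample size gives the number of patients who already have a condition. A model that predicts complications needs the number who will develop them during follow-up. The protocol supplies the first number and uses it to support both purposes.

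The count also belongs to the whole cohort. The sample size is said to rest on validation, yet validation and the Baveno VII comparison in held-out data will use only part of the 600.

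Two things are at stake. The statement that the events suffice, and the events-per-predictor assurance built on it, may be far too favourable for the complication target. And because CSPH and varices at entry are not excluded, a single mixed outcome would pool existing cases with later ones. Its AUROC could then not be read as early prediction.

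**Working it through.** **1. The plan's figure.** Events = N × prevalence. 600 × 0.24 = 144 and 600 × 0.47 = 282. Both reproduce exactly.

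**2. Incident complications.** The protocol gives no incidence. For complications to reach even the lower figure, the 24-month risk in all 600 would have to be 144 / 600 = 24%. Taking an assumed 24-month risk of 3% to 15%:

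- All 600: 600 × 0.03 = 18, up to 600 × 0.15 = 90.
- Patients free of CSPH at baseline, 600 × 0.53 = 318 to 600 × 0.76 = 456: 318 × 0.03 ≈ 10, up to 456 × 0.15 ≈ 68.
- Held-out set of an assumed 20% to 30% of all 600: 18 × 0.20 ≈ 4, up to 90 × 0.30 = 27.

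**3. Prevalent CSPH in a held-out set.** Cases = 600 × test fraction × prevalence, with an assumed test fraction of 15% to 30%. Precision uses the Hanley-McNeil standard error at A = 0.85, the protocol's benchmark, with n1 cases and n0 non-cases:

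SE² = [A(1−A) + (n1−1)(q1−A²) + (n0−1)(q2−A²)] / (n1·n0), where q1 = A/(2−A) and q2 = 2A²/(1+A). The half-width is 1.96 × SE.

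| Test fraction | Patients | Cases at 24% / 47% | SE | 95% half-width |
|---|---|---|---|---|
| 15% | 90 | 21.6 / 42.3 | 0.0547 / 0.0419 | 0.107 / 0.082 |
| 20% | 120 | 28.8 / 56.4 | 0.0473 / 0.0363 | 0.093 / 0.071 |
| 30% | 180 | 43.2 / 84.6 | 0.0386 / 0.0296 | 0.076 / 0.058 |
| All 600 | 600 | 144 / 282 | 0.0211 / 0.0161 | 0.041 / 0.032 |

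**4. What this means for a comparison of two AUROCs.** As an illustration only, take 0.85 against an assumed comparator of 0.80, a between-model correlation ρ of 0.3 to 0.7 (assumed) and the protocol's two-sided α of 0.05. Power is Φ(0.05/SD − 1.96), with SD² = SE1² + SE2² − 2ρ·SE1·SE2. It runs from 0.109 to 0.525 in a 15% to 30% test set, and from 0.472 to 0.959 with all 600.

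**5. The fairness criterion.** The Outcomes section sets equitable performance as "defined as an AUROC parity gap of no more than 5" percent. If a subgroup made up 10% to 30% (assumed) of a 120-patient test set, it would have 12 to 36 patients, and so about 12 × 0.24 ≈ 3 to 36 × 0.47 ≈ 17 prevalent cases. A point estimate of the gap means little at that size.

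**The case against.** The strongest reply is that the count fits a target the protocol does state. The sample-size section speaks of CSPH events, not complications; the Outcomes section lists CSPH; and the 0.85 benchmark is for identifying CSPH. For that purpose prevalence times N is the right kind of number. This stands, and it confines the first defect to the complication part of Aim 2.

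A second reply is that the section claims the count for development and validation together, never places 144 to 282 cases in the test set, and disclaims a conventional hypothesis-testing formula. So no power is promised, and the power figures above break no commitment. That also stands. But the section does claim sufficiency for judging improvement over Baveno VII, and does so with a whole-cohort count.

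Some stronger readings are tempting but are not supported by the document:

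- **Many prospective patients will have less than 24 months of follow-up.** A reader might infer this from "retrospective data extraction and prospective observational data collection expected to occur over approximately 24 months". The cohort mixes retrospective and prospective patients, no accrual schedule is given, and retrospective patients may have full follow-up. The handling of censoring can sit in an analysis plan.
- **The cited prevalence is inflated by decompensated patients.** This is possible, since this study excludes Child-Pugh B and C, but the protocol does not describe the cited cohorts in enough detail to show it.
- **A held-out split is the wrong design.** A patient-level split with tuning inside the training data is accepted practice. The objection is to the count quoted for it.
- **600 patients are too few.** The incidence, split fractions and number of predictors are not stated, so the document cannot settle this either way.

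**Conclusion.** The concern holds in two limited respects. First, 144 to 282 is a prevalent count and says nothing about how many incident complications will occur, although the protocol makes these all or part of the Aim 2 target. Second, it is a whole-cohort count offered in support of validation and a model comparison that will have only a fraction of it in held-out data.

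The first respect follows from the text alone; its size depends on the assumed 3% to 15% risk. The second also follows from the text; its size depends on the assumed 15% to 30% test fraction. Across that range the AUROC interval is about 1.8 to 2.6 times as wide as with all 600 (0.058 / 0.032 and 0.107 / 0.041). The arithmetic of the stated figure is correct, and the figure remains usable for cross-sectional identification of CSPH over development and validation combined.

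**What to change.** Before data collection starts, revise the sample-size section and the Aim 2 outcome:

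1. Define two targets: (a) prevalent CSPH at baseline, and (b) incident complications within a fixed horizon, among patients free of that complication at baseline.
2. Give the expected number of events for each, with a sourced incidence for (b), in total and in the held-out or external data, with the resulting AUROC precision.
3. Limit the sufficiency and events-per-predictor statements to what those counts support.
4. Report the 5% AUROC parity gap with its confidence interval.

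Resampling on all 600, or leave-one-site-out validation, would use more of the cases for assessing performance. It is an option to weigh against the planned split, not a necessary correction.

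The cost is rewording and a short calculation. The stated event counts become less favourable, most of all for complications. No extra patients are needed, and the Results section confirms that recruitment has not begun.
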